# Randomised controlled trial to evaluate the effectiveness of using the RD-1-based C-Tb skin test as a replacement for blood-based interferon-γ release assay for detection of, and initiation of preventive treatment for, tuberculosis infection: RID-TB:Dx study protocol

**DOI:** 10.1136/bmjopen-2021-050595

**Published:** 2021-12-30

**Keywords:** tuberculosis, clinical trials, diagnostic microbiology, preventive medicine

## Abstract

**Introduction:**

The predictive utility for incident tuberculosis (TB) of the purified protein derivative tuberculin skin test and region of difference 1 (RD1)-based interferon-gamma release assays (IGRA) is comparable; and either is recommended to test for latent TB infection (LTBI). Despite associated high costs of IGRA, sites participating in LTBI screening in many high-income settings pragmatically favour IGRA due to its higher specificity and simpler logistics. A new RD1-based skin test, C-Tb, could offer an acceptable and as accurate, cheaper alternative to IGRA. Evaluating the impact of C-Tb on process and patient-related outcomes would provide important information to help guide its use in LTBI testing strategies.

**Methods and analysis:**

This is a pragmatic multicentre, open-label, non-inferiority, randomised controlled trial. The trial will assess the initiation of LTBI treatment following a positive result of the randomised test as the primary outcome. Participants will be randomised to receive the C-Tb test (intervention) or IGRA (usual care, control) for initiation of treatment. We will enrol 1530 participants in England aged≥16 years who are eligible for LTBI testing and treatment according to UK guidance. In the C-Tb arm, skin induration will be assessed 2–3 days after intradermal injection and measured in millimetres of induration. Results of IGRA will be obtained in line with standard practice. Behavioural studies will explore people’s experiences, perspectives and preferences of LTBI testing and treatment. Economic analysis will estimate cost-effectiveness of changes to the diagnostic algorithm for LTBI. The protocol was developed with Patient and Public Involvement (PPI), which will continue throughout the trial.

**Ethics and dissemination:**

Ethics approval has been obtained from The NHS Health Research Authority (269485). We will share results of the trial in peer-reviewed journals and conferences.

**Trial registration number:**

EudraCT 2019-002592-34; ISRCTN17936038.

Strengths and limitations of this studyThis is the first trial to assess the impact of a novel C-Tb test on initiation of treatment for latent tuberculosis infection (LTBI) and process outcomes along the LTBI care cascade.Substudies will assess people’s experiences, perspectives and preferences of LTBI testing and treatment and estimate cost and cost-effectiveness of C-Tb, which provide additional evidence to guide testing algorithms.The trial will be conducted in England, largely in migrant populations and contacts of TB patients, and thus generalisability to other settings and populations may be limited.This is an open-label trial; knowing the allocation group might influence how clinicians manage participants offered preventive treatment.Initiation of LTBI treatment for the primary outcome will be based on prescription records.

## Introduction

Following major declines in tuberculosis (TB) incidence over most of the 20th century, there was a resurgence of the disease in the UK from the late 1980s to 2005,^1^ which then stabilised at relatively high levels but has been declining since 2011.^2^ In 2019, there were 4725 cases notified in England; an incidence of 8.4 cases per 100 000 population, still higher than most other Western European countries and three times as high as in the USA.^2^ TB disproportionately affects underprivileged communities, such as migrants and homeless people, with a higher incidence of disease and poorer outcomes associated with disadvantage. Addressing TB in these populations is critical for UK to achieve TB elimination.

The diagnosis and treatment of people diagnosed with latent TB infection (LTBI) can reduce the incidence of TB disease by halting progression of LTBI to TB disease, and consequently disrupting transmission in the community.^3^ LTBI screening and treatment for high risk groups such as new migrants from high TB incidence countries is thus recognised as an essential strategy to halt transmission in England.^4^

Currently available LTBI tests in England include the interferon-gamma release assays (IGRA) and the purified protein derivative tuberculin skin test (TST).^5^ The utility of the TST is limited by its poor specificity and sensitivity; and operational challenges.^6^ Its sensitivity and specificity were estimated to be 70% and 68%, respectively, in immunocompetent adults in a systematic review.^7^ IGRA while similar sensitivity for LTBI ranges 60%–80%, in contrast has specificity 90%–99%, depending on the population.^6 7^ Regardless of the differences in accuracy, head-to-head analyses in systematic reviews have shown the predictive performance for subsequent progression to active TB of the two tests to be comparable.^8 9^ Based on low-quality evidence, the WHO recommended that either test could be used for the diagnosis of LTBI in high-income low-incidence countries.^8 10^ The LTBI screening programme in the UK pragmatically offers IGRA to new migrants and other groups at high risk for TB infection and disease due to its higher specificity and relatively simpler logistics. The use of IGRA may lead to a smaller number of patients requiring treatment compared with TST without an increase in TB incidence in people who are not treated.^11^ Furthermore, IGRA does not require a return visit for evaluation of results within a specific time frame for results to remain valid, unlike TST. However, individuals who test positive on IGRA still currently need to return to care for TB investigations and initiation of preventive treatment. The use of IGRA as a primary test for TB infection follows the guidance in the 2016 National Institute for Health and Care Excellence guidelines for managing LTBI.^5^ Despite its apparent operational simplicity, blood-based detection of LTBI by IGRA is less cost-effective than TST.^12^ Moreover, although IGRA results could, in theory, be available on the same day, to offset costs, tests are run in batches every 5–14 days depending on local arrangements. This can result in delays in obtaining actionable results and eventual prescription of preventive treatment to eligible individuals, which offsets perceived advantages.

Statens Serum Institut has developed a new skin test (C-Tb), containing the recombinant antigens ESAT-6 (dimer) and CFP10 (monomer) derived from *Mycobacterium tuberculosis*. Similar to IGRA, and in contrast to the TST, C-Tb appears unaffected by previous BCG vaccination^13^ and HIV infection,^14^ both of which affect test performance of TST. Studies reported high overall concordance (94%), and similar sensitivity (74%) and specificity (96%) to the QuantiFERON-TB (QFT) Gold In Tube blood IGRA test.^15 16^ C-Tb could thus be an immunological improvement on the standard TST, and may therefore offer a cheaper, accurate and acceptable replacement or alternative to IGRA.^5^ However, there is no evidence of the impact of C-Tb use on patient and process outcomes along the LTBI care pathway from initiation to completion of treatment, or utility when used in current testing algorithms. In a previous study, participants at high risk for TB in an urban area in the US preferred initiation LTBI treatment based on TST results to those of the QFT Gold.^17^ While accuracy data alone are often used to register new diagnostic tools, any decision to replace a current tool with a new one should additionally consider the impact on patient-important outcomes evaluated in randomised studies.^18^

### Objectives

The overall aim of the RID-TB:DX trial is to evaluate whether C-Tb can be used as an alternative test to the interferon-gamma release assay in the screening of LTBI in England. The primary objective is to determine whether the proportion of participants initiating LTBI treatment based on C-Tb testing is at least as high as that based on the standard-of-care testing. The secondary objectives include: (1) to determine the safety of C-Tb test; (2) to determine the impact of C-Tb test on outcomes along the LTBI care pathway; (3) to evaluate the concordance and diagnostic accuracy of the C-Tb test compared with IGRA; (4) to assess modifiable behavioural factors influencing patient and provider engagement with LTBI testing (includes acceptability and other patient-important outcomes) and (5) to evaluate the cost-effectiveness and budget impact of combinations of new technologies to improve LTBI outcomes.

## Method and analysis

### Trial design

A multicentre open-label non-inferiority randomised controlled trial with two parallel groups, C-Tb testing versus standard-of-care testing (IGRA), with 1:1 allocation ratio (figure 1).

**Figure 1 F1:**
[figure not shown]
Trial schema. *IGRA test will also be done, as per usual care, with those testing C-Tb-negative but IGRA-positive being offered LTBI treatment; such patients who initiate treatment will not count as having achieved the primary endpoint. C-Tb assessors will be blinded to IGRA results. **On review on follow-up, test-negative individuals will be informed of their result and counselled on its interpretation. IGRA, interferon-gamma release assays; LTBI, latent tuberculosis infection.

### Study setting

The trial will recruit from primary and secondary care sites that implement systematic LTBI testing and treatment in England, UK. RID-TB: Diagnostics (Dx) is part of a 5-year programme of work (RID-TB) which is funded by the National Institute for Health Research (NIHR) (RP-PG-0217-20009 https://dev.fundingawards.nihr.ac.uk/award/RP-PG-0217-20009).

### Study population

The trial will enrol populations for which LTBI testing and treatment is recommended according to national guidance.^19^ The trial will largely recruit the priority risk groups for LTBI testing comprising individuals who are contacts of persons diagnosed with active TB and persons screened within the migrant screening programme.^19 20^ The LTBI migrant screening programme is for new migrants into the UK: individuals should be tested for LTBI if they are aged 16–35 years, entered the UK from a high incidence country (≥150/100 000) or Sub Saharan Africa within the last 5 years and been previously living in that high incidence country for 6 months or longer.^20^

#### Inclusion criteria

Age ≥16 years and ≤65 years.Eligible for LTBI testing with IGRA and treatment for LTBI according to UK guidance.Willing and able to provide written informed consent.Willing and able to comply with the trial, including the randomised test(s) and adherence to follow-up visits.

#### Exclusion criteria

Allergy to C-Tb product or any of its constituents.Displaying any symptoms or signs of active TB disease.Women who are breast feeding, pregnant or plan to become pregnant during the study.*Women of childbearing potential not using contraception.**At the time of writing, safety data on C-Tb in pregnant and breastfeeding women had not been assessed by the Medicines and Healthcare products Regulatory Agency. These criteria may be revisited once data become available.

### Interventions

Participants will be randomly allocated to the intervention arm, in which they receive the C-Tb test (Serum Institute of India, India) or the usual care arm, in which IGRA is offered as the test for LTBI. The latest generation QFT IGRA or T-SPOT.TB depending on practice at sites will be offered as the standard of care test (and from now on simply referred to as IGRA).

#### Intervention arm

Participants in the intervention arm will be managed based on C-Tb test results. C-Tb test is a skin test based on recombinant ESAT-6 and CFP10 C-Tb. The test will be administered intradermally according to the Mantoux technique.^16^ Participants will be monitored in clinic for up to 30 min after C-Tb administration. Skin induration will be assessed 2–3 days after placement; induration size of 5 mm or larger is defined as a positive reaction.^21^ Treatment of LTBI will be offered to those with a positive C-Tb result following a pretreatment assessment as per usual care (see below).

An IGRA will also be performed on all participants in the C-Tb arm in line with standard practice. Phlebotomy for IGRA will precede placement of C-Tb to avoid priming and boosting of results. Clinicians will be blinded to the IGRA result when C-Tb results are evaluated and the treatment decision is made. We will implement a study-specific standard operating procedure to ensure clinicians are blinded to the IGRA result in the rare event this is available at the time of the C-Tb reading. This scenario is highly unlikely since C-Tb results are read within 2–3 days of LTBI testing and IGRA results are obtained from designated labs up to 2–4 weeks following batch testing. Therefore, participants with positive C-Tb test results will be offered treatment before IGRA test results are disclosed. Any participants with IGRA-positive results, who have not yet been offered treatment based on a positive C-Tb result (ie, tested C-Tb negative, or unknown C-Tb result), will be assessed and offered TB preventive treatment as per usual care. Participants with positive C-Tb results but negative IGRA results who have already initiated treatment for LTBI will remain on LTBI treatment.

#### Control arm

Participants in the control arm will be tested with an IGRA alone as per usual care, and managed according to IGRA result. IGRA testing will be conducted using standardised local protocols and results will be interpreted as per manufacturer’s recommendations (cut-off for positivity 0.35 IU/L for QFT and eight spots for T-SPOT.TB). Results will be obtained within the usual time frame for that particular clinic/setting and discussed with the participant. Although time frames will be setting specific, we expect this to occur at week 4 (±2 weeks). Treatment of LTBI will be prescribed to those with positive IGRA results once TB disease is ruled out as per national guidance.^19^

#### Clinical assessments in usual care

Usual care in both arms comprises clinical assessment at baseline and during follow-up. This includes a brief review of medical history and symptom check and X-ray of the chest to rule out TB disease and further evaluation if this is suspected. Laboratory assessments may include blood testing for haematology, liver and kidney function tests, C reactive protein, HbA1c and glucose, and a blood-borne virus screen will be done for pretreatment assessment of LTBI-positive tests as appropriate within routine care, and may vary slightly by site. Participants with a positive test result either on the C-Tb or IGRA will be reviewed; a detailed history and clinical assessment will be performed, including chest radiography to rule out TB disease prior to initiation of LTBI treatment. The treatment regimen will be decided by attending clinicians according to national guidelines.^5^ Follow-up of treatment and assessment of completion will be done under usual care.

### Outcomes

#### Primary outcome

The primary outcome is initiation of LTBI treatment (within a defined 24±4 week follow-up period) based on a positive result of the randomised test (ie, C-Tb in the intervention arm and IGRA in the control arm). This will be based on all participants randomised so as to capture the overall impact of C-Tb versus IGRA testing on patient and operational processes. Participants in the C-Tb arm who did not initiate treatment based on a positive C-Tb result but started later based on a positive IGRA result will be considered not to have achieved the primary outcome.

#### Secondary outcomes

Safety: local and systemic reactions in participants randomised to the C-Tb test.Process outcomes related to impact on the LTBI pathway:For participants randomised to C-Tb, failure to return for C-Tb reading within 2–3 days as recommended by the manufacturer.Acceptance of LTBI treatment among participants with a positive result of the randomised test, as determined by verbal agreement.Initiation of LTBI treatment among those with a positive result of the randomised test, as determined by confirmation of LTBI treatment medications issued by pharmacy.Losses to follow-up between diagnosis with LTBI and starting LTBI treatment.Time (days) from testing to starting preventative therapy.Completion of LTBI treatment within a 24±4 week period from starting treatment.

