### Sample size

A total of 1530 participants will be recruited. This will provide the study 90% power to demonstrate non-inferiority of C-Tb compared with IGRA in terms of the proportion of participants initiating LTBI treatment based on their randomised test result, at 5% one-sided significance level (table 1).^22^ This is based on a non-inferiority margin of 6% for the absolute difference between arms, and assumes 20% of participants in the IGRA arm decide to start treatment.^23^ The non-inferiority margin can be reviewed if the event rate in the control arm differs from the original assumption within the non-inferiority frontier framework approach.^24^

**Table 1 T1:** Power calculations for the study assuming varying proportion of IGRA arm participants starting treatment*

	Proportion of participants in IGRA arm starting LTBI treatment		
	15%	20%	25%
Sample size required to achieve 90% power	1214	1524	1786
Power of study, with overall sample size=1530	95%	90%	86%

*Based on a non-inferiority margin of 6% for the absolute difference between IGRA versus C-Tb arm and 5% one-sided significance level.

IGRA, interferon-gamma release assays.

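### Treatment acceptance and initiation among randomised-test positives use denominators formed differently by arm: a C-Tb positive requires a return for reading, an IGRA positive does not

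*Protocol article*

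**What the plan says.** The process outcomes under Secondary outcomes include acceptance of treatment and "Initiation of LTBI treatment among those with a positive result of the randomised test". Both are restricted to participants positive on the test they were randomised to. Failure to return for the C-Tb reading is listed as a process outcome of its own. Loss to follow-up is worded differently: "Losses to follow-up between diagnosis with LTBI and starting LTBI treatment". Time to starting is counted from testing.

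The Intervention arm section makes a C-Tb positive depend on an induration of at least 5 mm, assessed two to three days after placement, and it foresees participants whose C-Tb result is unknown. For the control test, the Introduction says that "IGRA does not require a return visit for evaluation of results within a specific time frame for results to remain valid", but adds that IGRA positives must still come back for investigation and treatment.

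Every participant in the C-Tb arm also has an IGRA: "Phlebotomy for IGRA will precede placement of C-Tb to avoid priming and boosting of results". Those who are IGRA-positive but C-Tb-negative or unread are assessed and offered treatment as in usual care.

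The Primary analysis section says the primary result will be interpreted with the help of other components. It names acceptance and initiation among positives, concordance and diagnostic accuracy. The list is not closed, but non-return for reading is not on it.

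**The concern.** An IGRA positive who never comes back has a laboratory result, stays in the denominator and counts as not started. A participant in the C-Tb arm who would have been positive but never comes back has no C-Tb result and drops out of the denominator. One arm's positives have already shown that they attend; the other's have not. Randomisation does not make these two groups comparable.

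These proportions have a job to do. The second secondary objective is the impact of C-Tb along the care pathway, and the Primary analysis section relies on acceptance and initiation among positives to explain the primary result. If willingness to return and willingness to be treated go together, a reader could conclude that C-Tb improves uptake once positive when the difference is only selection. The two scales could even point in opposite directions, with C-Tb better among positives and worse among all randomised.

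**Working it through.** **The plan's own figure.** The Sample size section sets a "non-inferiority margin of 6% for the absolute difference between arms", "at 5% one-sided significance level", 90% power, and "assumes 20% of participants in the IGRA arm decide to start treatment". With unpooled variance and 1:1 allocation, n per arm = (1.645 + 1.282)² × 2 × 0.20 × 0.80 / 0.06² = 8.564 × 0.32 / 0.0036 = 761.2. This rounds up to 762, or 1524 in total, as in Table 1. The other totals (1214 at 15%, 1786 at 25%) and the powers at 1530 (95.0%, 90.1%, 85.7%) also reproduce. The sample size rests on all randomised participants, so this point does not touch it.

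**How the denominators form.**

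| Would-be positive who... | IGRA arm | C-Tb arm |
|---|---|---|
| returns and starts | in denominator, success | in denominator, success |
| returns, does not start | in denominator, failure | in denominator, failure |
| never returns | in denominator, failure | no C-Tb result, not in denominator |

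**Size.** The article gives no non-return rate and no initiation rate among positives, so the inputs below are assumptions. Let 70% of would-be positives start if told they are positive, in either arm. Let r be the share who do not return for reading, and p the initiation rate those people would have had. With equal test performance and no effect of the test on behaviour, the IGRA arm shows 70% and the C-Tb arm shows (0.70 − r × p) / (1 − r).

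| r | p | C-Tb proportion | Spurious difference |
|---|---|---|---|
| 5% | 50% | 0.675 / 0.95 = 71.1% | +1.1 points |
| 10% | 35% | 0.665 / 0.90 = 73.9% | +3.9 points |
| 15% | 20% | 0.670 / 0.85 = 78.8% | +8.8 points |
| 10% | 70% | 0.630 / 0.90 = 70.0% | 0 |

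The last row is the case where return is unrelated to willingness. If p exceeded 70%, the sign would turn against C-Tb.

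**Opposite signs.** In the middle case, starts among all would-be C-Tb positives are 0.90 × 0.739 = 66.5%, against 70% with IGRA. That is 3.5 points worse, while the outcome as defined shows 3.9 points better.

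**A second baseline.** Assume 25% positive and 80% initiation, which gives the plan's 20% (0.25 × 0.80). With 85% return and 50% initiation in non-returners, the C-Tb proportion is (0.80 − 0.15 × 0.50) / 0.85 = 85.3%, or 5.3 points better. Over all randomised it is 0.25 × 0.85 × 0.853 = 18.1%, or 1.9 points worse than 20%. At 90% return the spurious gain runs from 3.3 points (non-returners start at 50%) to 8.9 points (they never start).

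**Check of an alternative denominator.** IGRA-positive status is available in both arms and does not depend on the C-Tb reading. But if starts are counted as in the primary outcome, an IGRA-positive, C-Tb-negative participant cannot succeed. The Introduction cites 94% concordance. Assume 25% positivity and discordance split evenly: 3 / 25 = 12% of IGRA positives are C-Tb-negative. At 70% initiation this costs C-Tb 0.12 × 70 = 8.4 points. That comparison is therefore useful as a supplement but not as the main one.

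**The case against.** The best defence is that return, positivity and initiation are successive steps of a cascade, and conditioning each on the one before is ordinary description. The lost step is reported, the primary outcome counts every unread participant as not having started on C-Tb, and the plan says the components will be read together. This stands in part. Reporting non-return makes the selection visible, but it does not make the conditional proportions comparable between arms.

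It is also fair that the article states no between-arm analysis for these outcomes. That they will be compared is inferred from the objective on pathway impact and from their role in interpreting the primary result. The absence of a secondary analysis method from a condensed article is not part of this point.

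Three stronger readings are tempting and are not supported:

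- A reader might infer that loss to follow-up shares the same denominator and that an unread participant can never be diagnosed. The outcome runs from diagnosis, and the Intervention arm section lets an IGRA-positive participant with an unknown C-Tb result be assessed and offered treatment. What stands is narrower: a diagnosis made by C-Tb already includes one return visit, and the article does not say whether those diagnosed only by IGRA are counted.
- A reader might infer that time to starting is flawed in the same way. It is already counted from testing, and nothing says it is limited to starters.
- A reader might infer that these outcomes necessarily favour C-Tb. That depends on non-returners being less willing to start. This is plausible, since both steps require attendance, but the article does not show it. Some advantage could also be genuine, because the C-Tb result comes sooner.

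**Conclusion.** The point holds for acceptance and initiation among randomised-test positives. The asymmetry follows from the article's own definitions and needs no assumption. The direction and size do need assumptions: 1.1 to 8.8 points in favour of C-Tb over the 70% baseline scenarios with less willing non-returners, 3.9 in the middle case, and zero if return is unrelated to willingness. These figures illustrate the mechanism and do not predict the trial's result.

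The primary outcome, its analysis and the sample size are not affected. What is at risk is the explanation of the primary result, because the proportions chosen to explain it can differ between arms with no effect of the test on behaviour. The point concerns secondary outcomes, but it is worth settling before any comparison by arm.

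**What to change.** 1. Make any between-arm comparison of the cascade steps (read, positive, accepted, started) with all randomised participants as denominator.
2. Add a supplementary comparison of initiation among IGRA-positive participants in both arms. The blood is drawn in both arms and before C-Tb placement, so this status does not depend on the return for reading, apart from samples not taken or not interpretable. Show it twice: with starts counted as in the primary outcome, and with any start. State that the first also reflects C-Tb/IGRA discordance and that the second credits IGRA-driven starts to the C-Tb arm.
3. Keep the proportions among randomised-test positives as within-arm description, printed beside the non-return rate.
4. In the Primary analysis section, name non-return for reading among the components used to interpret the primary result.
5. For loss to follow-up, count from testing when comparing arms, not from a diagnosis that in the C-Tb arm may already require a return visit.

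The cost is analysis wording and a few extra tables. No new data, visits or participants are needed. The drawback is that the IGRA-positive comparison leaves out C-Tb-positive, IGRA-negative participants, who appear only in the all-randomised and descriptive tables.
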